### Aims

This study will assess the quality, effectiveness, and acceptability of the My Braces app and test the following primary hypothesis:

Using the full functionality of the My Braces app improves adherence to oral hygiene advice in patients undertaking fixed brace treatment.

The secondary hypothesis is as follows:

Using the full functionality of the My Braces app improves adherence to orthodontic treatment advice (reduction in fixed appliance breakages, missed and rescheduled appointments, treatment duration, number of appointments, and enamel demineralization).

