#### Recruitment

It is anticipated that recruitment will take approximately 18 months. Patients meeting the inclusion criteria and willing to participate in the trial will be randomized to one of the three study groups:

Group A will act as the control group and will be provided with standard treatment information (verbal and written) and access to the basic version 1 of the app with just a toothbrushing timer. The timer is necessary as the health behavior outcome is toothbrushing duration.

Group B will be provided with standard treatment information (verbal and written) and access to version 2 of the app, which has a toothbrushing timer and provides generic treatment information (a combination of images and text).

Group C will be provided with standard treatment information (verbal and written), and patients will have access to version 3 of the app; this group will have access to the full functionality of the app, which will allow patients to input their own personalized treatment information (including progress photographs), set goals, and develop plans for achieving these goals and will provide the patient and clinicians with appropriate dashboards to monitor progress.

It is important to include Group B, as this will allow the team to ascertain whether it is the personalization of the app content that confers any benefit over and above providing generic information via an app if a difference is found between Groups A and C.

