#### Data Collection

A complete data set will be collected at baseline, 3 months into treatment, 12 months into treatment, and at the end of treatment when the orthodontic appliances have been removed.

Two primary outcome measures have been selected, a health behavior outcome and a clinical outcome, as both are felt to be important. The outcome measures are timed toothbrush use and gingival bleeding scores (these scores indicate the amount of bleeding from the gums, where bleeding is an indicator of inadequate toothbrushing).

The secondary outcomes of interest are as follows: plaque scores, which indicate the amount of plaque on the teeth, where retention of plaque is an indicator of inadequate toothbrushing; number of fixed appliance breakages; number of missed and rescheduled appointments; treatment duration, number of appointments (including emergency appointments for appliance breakages); enamel demineralization (early tooth decay) on the upper anterior six teeth (using standardized photographs), as demineralization is a further indicator of inadequate toothbrushing and nonadherence to the appropriate diet; subjective quality of the app (sections E and F of the uMARS questionnaire); and app engagement.

The following baseline measurements and details will be obtained prior to treatment commencing: age, gender, malocclusion (type of dental bite), whether or not extractions (removal of teeth) are required for treatment, clinical photographs of the teeth (these will be compared with completion of treatment photographs to assess for enamel demineralization), bleeding score, and plaque score.

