#### Sample Size

The following assumptions have been made in the sample size calculation:

Data are normally distributed and initial comparison of the 3 groups would use an analysis of variance (ANOVA), followed by 2-sample *t* tests for A versus B, B versus C, and A versus C if any statistical significance is found.

The significance level is *P*<.05 with 80% power.

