#### Planned Analyses

Proposed outcome analyses are summarized in Table 2.

For each of the main outcome measures, it is anticipated that regression analysis will be undertaken. The main factor of interest (group allocation) and confounding variables (eg, age, gender, ethnicity) will be entered into univariable regression analyses to determine the level of significance and to limit the number of variables entered into the multivariable analysis. Any factors with *P*≤.10 will be considered for inclusion in the multivariable analysis. Factors with *P*<.05 in the multivariable analysis will be considered as having a significant effect on toothbrushing time or gingival bleeding. Secondary outcomes will be explored in a similar manner.

If necessary, an intention to treat analysis will be performed; all enrolled and randomized patients will be included in the analysis and analyzed in the groups to which they were randomized.

**Table 2 table2:** A summary of proposed statistics for outcome analysis.

Outcomes	Method of analysis
Toothbrushing duration	Comparison of the 3 groups using an ANOVA, followed by 2-sample *t* tests (A vs B, B vs C, and A vs C) if any statistical significance is found
Bleeding score	Chi-square test
Plaque scores	Comparison of the 3 groups using an ANOVA, followed by 2-sample *t* tests (A vs B, B vs C, and A vs C) if any statistical significance is found
Number of breakages	Kruskal-Wallis test, followed by Mann-Whitney test (A vs B, B vs C, and A vs C) if any statistical significance is found
Number of missed appointments	Kruskal-Wallis test, followed by Mann-Whitney test (A vs B, B vs C, and A vs C) if any statistical significance is found
Total number of appointments	Kruskal-Wallis test, followed by Mann-Whitney test (A vs B, B vs C, and A vs C) if any statistical significance is found
Treatment duration	Comparison of the 3 groups using an ANOVA, followed by 2-sample *t* tests (A vs B, B vs C, and A vs C) if any statistical significance is found
Enamel demineralization	Chi-square test
App subjective quality	Comparison of the 3 groups and different section of the uMARS form by using the Kruskal-Wallis test.
App engagement	Comparison of the 3 groups using an ANOVA, followed by 2-sample *t* tests (A vs B, B vs C, and A vs C) if any statistical significance is found

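### The primary hypothesis is about the full app (Group C), but the planned ANOVA gate with three equal follow-up pairs is not aimed at C versus A and gives that contrast less power than the same patients could

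*Protocol article*

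**What the plan says.** All references are to the protocol article.

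- **Aims.** There is one primary hypothesis: "Using the full functionality of the My Braces app improves adherence to oral hygiene advice in patients undertaking fixed brace treatment".
- **Recruitment (Phase 2).** Of Group C it says "this group will have access to the full functionality of the app". Groups A and B get reduced versions. Group B is there to show whether personalization adds benefit "over and above providing generic information via an app if a difference is found between Groups A and C". That puts A versus C first and uses B to interpret it.
- **Data Collection (Phase 2).** "Two primary outcome measures have been selected, a health behavior outcome and a clinical outcome": timed toothbrush use and gingival bleeding.
- **Sample Size.** For both outcomes the assumed scheme is a three-arm ANOVA as the opening step, with pairwise t tests to follow: "A versus B, B versus C, and A versus C if any statistical significance is found".
- **Planned Analyses, Table 2.** Toothbrushing duration has the same scheme: "Comparison of the 3 groups using an ANOVA, followed by 2-sample" t tests on the three pairs. The bleeding row says only "Chi-square test".
- **Planned Analyses, text.** A regression is also planned. Group allocation enters as one factor and is judged at P<.05, with no contrast between arms named.

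**The concern.** The hypothesis and the arm rationale both point to C versus A. The analysis starts with a test of any difference among three arms and then gives A versus B, B versus C and A versus C equal standing. The regression rule has the same gap, because a significant three-level group factor does not say which arm differs.

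Two things follow. First, a significant omnibus test or group factor does not by itself bear on the stated hypothesis, since it also arises when only B differs. Second, alpha and power are spent on comparisons that the Aims do not ask about. The contrast that the trial was set up for is then tested less sensitively than the same patients would allow, most of all when B lies between A and C, which is a natural expectation for nested app versions.

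**Working it through.** **Inputs.** Standardized differences 0.85 (toothbrushing, 20 s over SD 23.6 s) and 0.75 (bleeding, 15% over SD 20%), 29 and 38 evaluable per group, 80% power and the .05 level are all from Sample Size. I assume two-sided tests, normal data, equal variances and equal arms.

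**1. Reproducing the stated sizes.** The article allows for multiple testing without naming a method. Bonferroni over three pairs reproduces its figures:

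n = 2 × ((z for .05/3 + z for 80% power) / d)² = 2 × ((2.394 + 0.842) / d)²

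- d = 0.85: 28.98, rounded up to 29.
- d = 0.75: 37.22, rounded up to 38.

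The trial is therefore sized on a pairwise t test at about .0167, with alpha spread equally over three pairs. It is not sized on the omnibus test or on a single lead contrast.

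**2. Power for A versus C tested directly.** Two-sample t test with 2n − 2 degrees of freedom and noncentrality d × √(n/2).

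- n = 38, d = 0.75: noncentrality 3.27, power 89.7% at .05.
- n = 38, d = 0.85: noncentrality 3.71, power about 95.5% at .05.

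**3. Power for A versus C behind the gate.** With B midway, the omnibus noncentrality is n × d²/2. For n = 38 and d = 0.75 this is 38 × 0.5625 / 2 = 10.7, and the omnibus power is 83%. The joint event (omnibus P<.05 and A versus C significant) was simulated with 400,000 trials per scenario.

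| Scenario, B midway | Direct at .05 | Gate, pairs at .05 | Gate, pairs at .05/3 |
|---|---|---|---|
| n = 38, d = 0.75 | 90% | 82% | 78% |
| n = 38, d = 0.85 | 95.5% | 91% | 89% |
| n = 29, d = 0.85 | 89% | 81% | 77% |

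The last row uses the evaluable number from the toothbrushing calculation. The trial recruits to the larger bleeding requirement, so the n = 38 rows are closer to what it will have (46 × 0.8 = 36.8 per group).

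**4. Where the loss comes from.** With unadjusted pairs, all of it is the gate: about 7 points at n = 38, d = 0.75. With pairs at .05/3, the gate itself removes less than 1 point (79.2% to 78.4%). The rest of the roughly 11-point shortfall is alpha given to two pairs that the primary hypothesis does not concern.

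**5. Sensitivity to B.** If B equals A or equals C, the gate with unadjusted pairs costs about 2 points at n = 38, d = 0.75 (89.7% to 87.5%) and about 1 point at d = 0.85.

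**6. What the omnibus test responds to.** If only B works (C equal to A, B shifted by 0.75, n = 38), the omnibus test is significant in about 93% of trials, while A versus C reaches P<.05 in about 5%.

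**7. Power with C versus A named.** At .05, 80% power needs 23 (toothbrushing) and 29 (bleeding) evaluable per arm by t test. At .025 each, it needs 28 and 36. All are within the planned 29 and 38, at which C versus A has about 82% and 83% power at .025.

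**The case against.** **A false-positive route is not in the text.** From step 6 a reader might infer that A versus B alone could make the trial positive. The document does not support that. It nowhere says that a significant ANOVA, or any one significant pair, establishes the hypothesis. Aims ties the hypothesis to the full app, and Table 2 requires A versus C to be tested after a significant ANOVA. If only B worked, that step would usually show no A–C difference, and the omnibus result would be a correct detection of B's effect. This objection stands.

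**The gate is a recognised method.** With exactly three groups, an omnibus test followed by unadjusted pairs controls the familywise error within one outcome. This also stands: the gate is valid as error control, and the fault is that it does not fit the hypothesis.

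**The size is conditional.** B midway is the least favourable of the positions checked, and at d = 0.85 with 38 per arm the gated power remains well above 80%. This stands too, and the figures must be given with those conditions.

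**The deciding test is not settled.** Table 2 applies ANOVA to only one primary outcome, lists bleeding under a chi-square test, and sits beside a regression with its own rule. So the gate applies to bleeding only through the Sample Size assumptions. The missing contrast, however, is common to all three routes.

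**It may be in the analysis plan.** A condensed article can leave a testing order to another document. Here the article does fix a procedure, in two places, and what it fixes is not directed at its own hypothesis. This objection does not remove the point.

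**Conclusion.** The point holds as a mismatch between hypothesis and analysis. The primary hypothesis concerns Group C, and the arm rationale leads with A versus C, yet the stated procedure treats three pairs alike behind an omnibus gate. Under two-sided tests on normal data with equal arms and B midway, at 38 per arm this costs A versus C:

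- about 7 to 11 points of power at d = 0.75;
- about 4 to 7 points at d = 0.85.

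The lower figure in each range is for unadjusted pairs and the higher for pairs at .05/3. With unadjusted pairs the cost is only about 1 to 2 points if B equals A or C. There is no basis for saying that the plan would declare success on A versus B. What can be said is that a significant omnibus test or group factor would not by itself support the primary hypothesis, and the plan should say what would.

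**What to change.** For each primary outcome:

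1. Name C versus A as the primary contrast and test it directly, without the omnibus gate.
2. If it is significant, test C versus B at the same level. This fixed sequence follows the order in Recruitment and needs no further adjustment across arms.
3. Report A versus B and the omnibus test as descriptive.
4. State that the primary hypothesis is judged on C versus A.

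Use the same C versus A contrast in the regression and in the bleeding analysis. The chi-square entry for bleeding in Table 2 must be reconciled with the ANOVA and t tests assumed in Sample Size.

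Also state whether one or both primary outcomes must succeed, and how they share alpha. If either one suffices and each is tested at .05, the chance of at least one false positive is up to 1 − 0.95² = 9.75% for independent outcomes. Splitting to .025 each leaves about 82% to 83% power at 29 and 38 evaluable per arm. That split uses up most of the gain over the gate with unadjusted pairs, but a gated plan would face the same charge.

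The cost is wording in Planned Analyses, Table 2 and Sample Size, with no extra patients. A versus B loses confirmatory status, which no hypothesis in Aims needs. The article reports no patients recruited at the time of writing; the change should be made before outcome data are seen.

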#### Planned Analyses

The Kruskal-Wallis test will be used to compare the uMARS scores across the three groups and the scores across different sections of the uMARS form.

Any changes felt to be appropriate based on feedback from the uMARS questionnaire will be implemented in the app prior to using it in phase 2.

### Phase 2

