##### Gingival (Gum) Bleeding

A periodontal probe (specialized probe to test gum health) will be used; the presence of bleeding within 10 to 30 seconds of probing is indicative of inflammation of the gingivae (gums). Scores will be recorded for all teeth anterior to the molars (incisors, canines, and premolars) and will be recorded as the percentage of the total number of tooth surfaces (6 surfaces per tooth). A binary score will be assigned to each surface (1 for bleeding present, 0 for no bleeding).

A calibration exercise will be conducted prior to commencing the study. The key factors affecting consistency of probing technique are probe position and pressure applied (ideally 20 to 25 grams). The bleeding assessment technique will therefore be reviewed and observed in a volunteer subject by a gold standard examiner following training performed on models. It is not possible to do duplicate bleeding assessments as the act of repeated probing can cause bleeding; therefore, it is essential that this aspect of the study is well controlled for.

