##### Gingival Bleeding

An estimated clinically relevant difference of 15% and a SD of 20% (standardized difference=0.75) was used, based on advice from [name] (clinical trials coordinator, Restorative Dental Sciences, UCL Eastman Dental Institute, Faculty of Medical Sciences, UCL), who has experience in commercial trials using these outcome measures. The same assumptions were followed as described above, and this indicated a sample size of 38 per group. With the 20% dropout factored in, the sample size calculation is 46 per group (n=138).

Therefore, 138 patients will be recruited. There are a number of assumptions in these calculations; therefore, an internal pilot will be conducted, and the calculations will be repeated using 3-month data for the first 15 patients recruited to each group.

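### Table 2 gives a chi-square test to gingival bleeding, a primary outcome that the protocol defines as a per-patient percentage and sizes as a comparison of means

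*Protocol article*

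**What the plan says.** Under Data Collection (phase 2), the protocol article names two primary outcomes: "The outcome measures are timed toothbrush use and gingival bleeding scores".

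Under Gingival (Gum) Bleeding, each tooth surface is scored 0 or 1 ("A binary score will be assigned to each surface (1 for bleeding present, 0 for no bleeding"), and the scores "will be recorded as the percentage of the total number of tooth surfaces (6 surfaces per tooth". The result is one percentage per patient.

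Under Sample Size, the stated assumption is "Data are normally distributed and initial comparison of the 3 groups would use an analysis of variance (ANOVA", with pairwise t tests to follow. For bleeding, "An estimated clinically relevant difference of 15% and a SD of 20% (standardized difference=0.75) was used". The same assumptions give 38 per group, raised to 46 for dropout. This larger of the two calculations sets the total of 138.

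Table 2, under Planned Analyses, then has the entry "Bleeding score Chi-square test". It gives no cut-point, no categories and no pairwise step. The plaque row gives ANOVA followed by t tests, although plaque is also a percentage of surfaces built from a 0/1 score per surface.

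The text above Table 2 also anticipates a regression for each main outcome, with group as the main factor and a P<.05 rule that names gingival bleeding. It does not give the type of regression.

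**The concern.** A chi-square test compares counts in categories. A percentage that varies continuously between patients has no categories until someone creates them. As the protocol stands, there are two ways to apply the test: divide patients by a cut-point that is not defined, or count the individual tooth surfaces as if each were an independent observation.

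The first discards information and leaves the cut-point open to choice after the data are seen. The second ignores that surfaces within one mouth resemble each other. Neither is the analysis that produced 38 per group. Bleeding is a primary outcome and drives the total sample size, so a mismatch here bears on the stated power of the trial.

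**Working it through.** **Inputs from the protocol article.** Difference 15 points, SD 20, so d = 15/20 = 0.75; power 80%; significance level 0.05 with an unnamed allowance for multiple testing; 38 evaluable per group.

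**Step 1: reproduce the stated figure.** Take three pairwise comparisons, two-sided alpha 0.05/3 = 0.0167 (z = 2.394) and power 80% (z = 0.842).

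n = 2 × (2.394 + 0.842)² / 0.75² = 37.2, rounded up to 38 per group.

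This matches. The same formula with d = 0.85 gives 29.0, the protocol's figure for toothbrushing. Uncorrected alpha 0.05 would give 28 for bleeding, not 38. The 38 is thus a comparison of means at alpha 0.0167. At 38 per group the power is 81% by this normal approximation and 79% by the noncentral t distribution (90% at alpha 0.05 by either).

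The figure cannot be recovered by reading 15% as a difference between proportions of patients. With one proportion between 30% and 60% and the other 15 points lower, 161 to 232 per group would be needed.

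**Step 2: chi-square on patients split at a cut-point.** For two normal groups 0.75 SD apart, the best cut is midway. The proportions above it are Φ(0.375) = 0.646 and Φ(−0.375) = 0.354, a difference of 0.292. At 38 per group:

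- SE under the null: √(2 × 0.25/38) = 0.1147
- SE under the alternative: √(2 × 0.646 × 0.354/38) = 0.1097
- Power at 0.0167: Φ((0.292 − 2.394 × 0.1147)/0.1097) = Φ(0.16) = 56%
- Power at 0.05: Φ((0.292 − 1.960 × 0.1147)/0.1097) = Φ(0.61) = 73%

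For 80% power at 0.0167 the best cut needs 60 per group. Other cuts do worse:

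| Cut, in SD from the midpoint | Proportions | Power at 0.0167 | Power at 0.05 |
|---|---|---|---|
| 0 | 0.646 v 0.354 | 56% | 73% |
| 0.375 | 0.500 v 0.227 | 54% | 71% |
| 0.75 | 0.354 v 0.130 | 45% | 63% |
| 1.5 | 0.130 v 0.030 | 21% | 36% |

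For the three-group test at 0.05, a central cut gives 62% to 75% power, against 83% to 93% for ANOVA. The range covers group means of 0/7.5/15 and 0/0/15.

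**Step 3: chi-square on pooled surfaces.** Assumptions not in the document: 16 to 20 teeth, so S = 96 to 120 surfaces per patient, and mean bleeding μ of 30% to 50%. The SD of 20 points between patient percentages is the protocol's. The design effect is the actual variance of a patient's percentage divided by its binomial variance:

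D = 0.20² × S / (μ(1 − μ))

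- μ = 0.5, S = 96: D = 0.04 × 96/0.25 = 15.4
- μ = 0.3, S = 120: D = 0.04 × 120/0.21 = 22.9

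With no true difference, the three-group statistic is inflated by about D, so P(reject) ≈ exp(−5.991/(2D)). That is exp(−0.195) = 82% for D = 15.4 and exp(−0.131) = 88% for D = 22.9. Beta-binomial simulation with 38 patients per arm gives the same 82% to 88%. ANOVA on the patient percentages from the same simulated data rejects about 5% of the time.

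**The case against.** The strongest reply is that Table 2 does not stand alone. The regression paragraph carries an explicit significance rule for gingival bleeding, and a linear regression on the percentage would be a sound analysis. A reader might infer from Table 2 that the primary analysis is simply invalid. The document does not support that much. What stands is that the regression is only anticipated, its type is not given, and nothing says whether it or the Table 2 test decides the primary result.

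A reader might also infer that the trial will produce false positives most of the time. Nothing says that surfaces will be pooled; the outcome section reduces them to a percentage, and the SD used for sizing belongs to that percentage. The 82% to 88% holds only under that reading and the assumed surface counts and means.

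The power loss is conditional too. Table 2 states no corrected alpha. At 0.05 with the best cut, the shortfall from 80% is about 7 points, and with all 46 per group evaluable the same formula gives about 81%. The large shortfall belongs to the alpha used for sizing, or to a poorer cut.

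The row "Enamel demineralization Chi-square test" invites a similar charge, that teeth within a patient would be treated as independent. The document does not state the unit of analysis, and a chi-square on one category per patient would be valid, so that charge is not made.

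It could be said that an analysis plan will settle the detail. But the protocol does not leave the test open: it names one that disagrees with its own definition and sizing.

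**Conclusion.** The point holds as an internal contradiction. The bleeding row of Table 2 does not fit the outcome definition, the sample size calculation or the parallel plaque row, and the regression paragraph does not resolve it. The contradiction needs no assumption.

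Its consequences are conditional. If patients are dichotomised, pairwise power at 38 per group is at most about 56% at alpha 0.0167 or about 73% at 0.05, assuming normal percentages with the protocol's difference and SD. If surfaces are pooled, the three-group type I error is about 82% to 88% under the surface counts and means assumed above. It should be corrected because it concerns a primary outcome and the one that sets the total of 138.

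A minor secondary point: the phase 1 plan uses Kruskal-Wallis to "compare the uMARS scores across the three groups and the scores across different sections of the uMARS form", and Table 2 repeats this for app subjective quality. Sections rated by the same respondent are not independent samples. With positive correlation between sections the test becomes conservative, so the cost is lost power, not false positives.

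**What to change.** Replace the chi-square entry for bleeding in Table 2 with a comparison of per-patient bleeding percentages. The minimum change is ANOVA followed by pairwise t tests at the multiplicity-adjusted level used for sizing (0.05/3 reproduces the 38), with that level written down. Preferable is a linear model with group and baseline bleeding, which is already collected, reporting mean differences with 95% confidence intervals.

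State which analysis is primary. If it is the regression described above Table 2, say that it is linear on the percentage and make the table agree. Treat plaque the same way; if the baseline-adjusted model is adopted, the plaque row changes as well.

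For comparisons between uMARS sections, use the Friedman test, and keep Kruskal-Wallis for comparisons between groups.

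The cost is a few lines of text, with no new data and no added patient burden. It is best done before the 3-month data on the first 15 patients per group are examined.
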